### Intervention

Light-weight oxygen gas cylinders will be used to provide oxygen during activities (ambulatory oxygen). Ambulatory oxygen will be provided by the relevant oxygen companies in the UK, through submission of a Home Oxygen Order Form (HOOF) based on the location of the patient participating in the study. Overall, there are four oxygen companies which provide supplemental oxygen in the UK, including Air Liquide (which services North and South London, North and South West England, and the East Midlands), BOC (Eastern England and NorthEast), Baywater Healthcare (Yorkshire and Humberside, West Midlands and Wales) and Dolby Vivisol (South Central England and South East Coast). Continuous oxygen flow via nasal cannulae will be used for all patients to standardise mode of delivery. Oxygen flow rates will be determined on the basis of the entry 6MWT on oxygen, so as to maintain oxygen saturation of ≥90% for at least half of the 6MWT, where possible. If the patients are randomised to start on oxygen on the first 2 weeks of the 4-week trial period, the company will be asked to remove any unused oxygen cylinders on the day of the crossover to the 2 weeks ‘off’ oxygen. To determine oxygen use during the 2 weeks when patients are randomised to be on treatment, patients will be asked to keep a daily diary recording the number of hours spent using oxygen. Investigators will also ask the relevant oxygen company to provide the number of cylinders delivered to the patient per week along with the number of any unused or partially used cylinders (approximating to the nearest 25%) at the end of the 2 weeks on oxygen, wherever possible. To further validate patient-reported use of oxygen cylinders, a researcher at the Aintree site will sample 10 consecutive patients living in the nearby area and will visit patients at home at the end of the 2 weeks of ambulatory oxygen to independently assess numbers of fully used, half-used and full oxygen cylinders. Comparison between patient- and researcher-reported cylinders use will be included in data analysis. More information is provided in Section 13 of the study protocol.

The study design does not include a placebo arm because:The intervention is a combination of possible benefits from oxygen and the disadvantage of canister weight. These cannot be separated. Placebo control is impossible because there is no means of providing placebo weight. Attempts to control solely for oxygen use without taking canister weight into account would not be clinically meaningful. In a recent COPD study, cylinder weight was reported as a barrier to use by 93% of study participants [22]A positive result against an air-filled canister arm would be clinically uninterpretable. This is a study design in which the ‘placebo’ would be actively harmful to study participants. Carriage of an air-filled cylinder would be expected to lead to earlier desaturation and reduced exercise tolerance. Such a design would not inform the real-life comparison between oxygen plus cylinder and no interventionIt should also be stressed that objective measures of change will be evaluated as secondary endpoints: we expect to explore correlations between these variables and the primary endpoint to exclude the possibility that an observed treatment benefit on the primary endpoint might be confounded by a placebo effect

### Concomitant medication

It will be possible to introduce any rescue medication during the study period as judged appropriate by the treating physician. However, the aim is to enrol subjects whose treatment is not expected to change during the 4-week treatment period of the trial. Patients who are on established treatment for their ILD, with immunosuppressants, corticosteroids, N-Acetyl Cysteine (NAC) and/or antifibrotic agents, will continue on their regular medication. Concomitant medication will be recorded in patient’s notes and the Case Report Forms (CRFs).

## Outcomes

### Primary outcome measure

Difference in the health status measured by the K-BILD (global score and its three domains) [16] between the two treatment arms (ambulatory oxygen versus no oxygen) at the end of the relevant treatment period

### Key secondary outcome measures

Difference in the UCSD Shortness of Breath Questionnaire at the end of each treatment period (oxygen versus no oxygen) [17]Difference in global patient assessment scores [18]

### Additional secondary outcome measures

Difference in health-related quality of life scores (SGRQ, HDAS) [19]Difference in activity parameter scores (SenseWear Armbands)Difference in patient-reported activity levels as per patient daily diariesDifference in the 48-h oxygen saturation scores recorded by portable oximeters (to be also used as an indirect measure of compliance)Difference in the 48-h oximeter recorded heart rateAnalyses on the placebo-controlled 6MWT on oxygen versus placebo air cylinders to assess whether the response to oxygen on the 6MWT predicts benefit of ambulatory oxygen in day-to-day lifeOxygen cylinder useSafety and tolerability

### Explanatory outcome measures

Benefit of ambulatory oxygen in relation to the following:o Improvement in baseline 6MWT performance on oxygen (at the flow determined during the screening visit) compared to placebo airo Outcome in relation to underlying ILD diagnosis: IPF versus non-IPFo Outcome in relation to the presence of pulmonary vascular disease/pulmonary hypertension (PH), defined on the basis of baseline echocardiogram (right ventricular systolic pressure (RVSP) >40 mmHg and/or right ventricular (RV) dilatation/reduced function) and/or elevated baseline serum BNP levels

### Qualitative interviews

The use of semistructured interviews in a subset of patients at the end of the study is aimed at identifying patient-derived expectations and concerns over the psychological and practical barriers faced when using ambulatory oxygen.

### Participant timeline

The time schedule for the enrolment, interventions and assessments for participants is shown in Additional file 2: Figure S1 and in Fig. 1. An indexed Standard Protocol Items: Recommendations for Interventional Trials (SPIRIT) Checklist can be found in Additional file 6.

**Fig. 1 Fig1:**
[figure not shown]
SPIRIT Schedule of Events

### Assignment of interventions

Randomisation allocation as to the order of treatment will be released using an interactive web-based randomisation system (InForm), set up by Imperial College Clinical Trials Unit (ICTU). Simple, block-method randomisation will be performed to determine the order of treatment.

All study patients will be randomised during baseline visit as follows:Randomisation as to the order in which subjects will perform the 6MWT on oxygen versus air. The patients will be blind to the content of the canistersRandomisation as to the order in which subjects will have the portable home oxygen versus no oxygen during the first 2 weeks of treatment

### Sample size estimate

As stated above, the primary outcome measure is the difference between the health status score measured by the K-BILD collected after 2 weeks on ambulatory oxygen and the K-BILD collected after 2 weeks on no oxygen. The repeatability of the K-BILD at 2 weeks in patients with stable ILD is high, with an intraclass coefficient for domains and total score of 0.86–0.94 [16]. This study is powered to detect a difference of 8 units in the K-BILD total score, the minimally clinically important difference (SD, 20), recently estimated [23].

We calculated that a sample size of 80 randomised patients would allow 90% power at 5% significance to detect a difference of at least 8 points between the two crossover trial arms, allowing for a 15% dropout rate, in view of the high morbidity/mortality of the disease. This degree of power will also allow us to perform some explanatory subgroup analyses, as out lined above. Although the study is powered to allow a 15% dropout rate, we will make every effort to minimise patient loss and missing data during the trial period [24]. In order to maximise completeness of data, patients will be called at the end of each week during the trial period. They will be reminded to wear the activity monitor and/or the oximeter for the allocated time, and will be encouraged to continue filling in their daily activity diaries. The software used for power calculations was ‘PS Power and Sample Size calculator version 3.0 by William Dupont and Walton Plummer 2009’. For the qualitative component, it is anticipated that a subsample of *N* = 20 will be adequate to achieve theoretical saturation.

### Data collection and management

#### Quality of life/Shortness of Breath Questionnaire data

The primary outcome measurement will be the difference in K-BILD scores on completion of the 2 weeks on ambulatory oxygen compared to no oxygen. All questionnaires will be self-administered during the study visits, and will be completed at baseline and repeated at the follow-up crossover visit after 2 weeks since the baseline visit and at the final follow-up visit at 4 weeks. In addition to the K-BILD, patients will be asked to complete the UCSD SOBQ [17], a widely validated index, designed to assess activity-related dyspnoea, as well as the global patient assessment of change [18], the SGRQ [19] and the HADS, both validated in ILD [20].

#### Activity assessment

During the second week of each of the 2-week periods of the study treatment, patients will be asked to wear an activity monitor during waking hours, the SenseWear Armband (Bodymedia – Pittsburgh, PA, USA), which measures energy expenditure, daily number of steps, and time spent at different levels of physical activity. SenseWear-derived measurements are sensitive and repeatable in patients with chronic lung disease [25, 26]. Patients will also be asked to complete a diary of daily activities as measure of physical activity by using a custom designed diary modelled on a modified diary method of Follick et al. [27, 28]. Participants will be asked to complete this diary at least three times a day, recording the activity undertaken for the majority of each 2-h block, in addition to specifying whether oxygen cylinders were used. In addition, total hours of outings each day will be recorded.

#### Oxygen saturation

For 48 h during the second week of each treatment period, patients will also be asked to wear a portable oximeter to assess oxygen saturation for 48 continuous hours. Measures of continuous oxygen saturation will also allow control for self-reported use of ambulatory oxygen.

At the end of each 2-week treatment period, the SenseWear Armbands, the oximeters and the patient diaries will be collected.

### Assessment of compliance of oxygen cylinder use

Oxygen use will be expressed as number of full, half-full and unused cylinders as self-reported by the patient after each of the 2 weeks on oxygen. Patient-reported use will be cross-checked by assessing accountability records provided by the relevant oxygen company, following an agreement that has been put in place.

To validate patient-reported use of oxygen cylinders, a researcher at the Aintree site will sample 10 consecutive patients living in the nearby area. The researcher will visit patients at home at the end of the 2 weeks of ambulatory oxygen to independently assess numbers of fully used, half-used and full oxygen cylinders. Comparison between patient- and researcher-reported cylinders use will be included in data analysis.

Patients will also be asked to fill in a daily oxygen use diary card to write down the time of use of oxygen canisters, and the activity being performed. This will be cross-checked with the continuous oxygen saturation data recorded by the portable oximeter, which patients will be asked to wear for 2 days a week, so as to correlate the two.

### Qualitative assessments

The impact of using ambulatory oxygen will be identified through qualitative semistructured interviews with a purposive sample of 20 patients. The interviews will explore patients’ and their informal carers’ perspectives on how the ambulatory oxygen has affected their day to day life. The interview will be conducted within 2 weeks of the end of treatment visit. Patients from the RBH site will be approached by a qualitative researcher at the end of treatment visit and asked if they will participate in the qualitative interview (as described in the Patient Information Sheet – Additional file 4). Consent of the patient and carer will be confirmed before proceeding to the interviews at a venue convenient to the patient.

The audio-recorded, semistructured interviews will use a topic guide focussing on practical barriers to optimal oxygen usage, practical, social and psychological difficulties encountered, concerns about dependency, and views on the information required prior to ambulatory oxygen prescription. The interviews will also explore patients’ experience of participating in the trial. Field notes will be written after each interview to aid reflexive analytical processes [29]. These interviews will also allow patients to provide suggestions on how to improve the provision and future design of ambulatory oxygen provision and devices as well as their views on the trial design.

### Safety assessments

Checking for the occurrence of adverse events and clinical endpoints will begin from randomisation and will continue until study completion. At each study visit the investigator or designee will make an assessment of safety and will specifically review the clinical history and investigation findings with regard to the occurrence of adverse events (AEs) or serious adverse events (SAEs). Details of adverse and clinical events will be captured on the trial electronic Case Report Form (eCRF).

### Blood samples

Blood samples will be taken at the start of the 4-week period to evaluate serum BNP levels. All BNP measurements will be performed in the same laboratory at the RBH.

### Health economics

The AmbOx study will include an economic evaluation to assess the cost-effectiveness of ambulatory oxygen use in patients diagnosed with fibrotic ILD compared to no ambulatory oxygen, from the perspective of the NHS. As ambulatory oxygen is not anticipated to have any effect on disease progression in the short term, costs related to unplanned health professional appointments or hospital admissions will not be included. The primary measure of benefit for the economic evaluation will be change in K-BILD score. Quality of life benefits will also be assessed using quality-adjusted life years (QALYs). QALYs will be estimated by synthesising utility values from existing medical literature for health states described by the K-BILD or SGRQ. Discounting will not be applied given the short trial duration. Cost-effectiveness will be expressed as the incremental cost per unit improvement in K-BILD and per QALY gained.

We expect that ambulatory oxygen will allow patients to lead an active and independent life for longer, with a varied set of longer-term benefits, reducing the period of dependency and expensive care packages associated with the final stages of fibrotic ILD, characterised by severely limited mobility. Therefore, future research should consider modelling the longer-term costs and benefits of ambulatory oxygen when sufficient data are available to evidence this potential benefit. The economic evaluation conducted alongside this trial will provide important preliminary guidance on the likely cost-effectiveness of implementing ambulatory oxygen in fibrotic ILD, as well as evidence to support future studies that extrapolate findings to a longer time horizon.

### Discontinuation or withdrawal of study subjects

We do not expect there to be any significant toxicity from the use of ambulatory oxygen. Subjects will be withdrawn from the trial only if they wish to do so, or if they develop an unexpected worsening in their condition which means that they require oxygen at rest. Patients withdrawing from the study will be asked, if willing and whenever possible, to fill in the relevant questionnaires at the end of the 2- and 4-week period, if needed via telephone, so as to be able to compare change in health status and other questionnaire-related outcomes, compared to baseline, against subjects completing the trial.

### Adverse event (AE) and serious adverse event (SAE) reporting

AEs and SAEs will be identified according to standard criteria and will be recorded in the eCRF and reported to the sponsor. Given the nature of the participants’ underlying disease, expected AEs and SAEs include disease progression, lower respiratory tract infections, hospitalisation, and death.

### Data management and data checking

Data will be collected on an eCRF system. The InForm system will be used to develop the eCRF and will be designed in accordance with the requirements of the clinical trial protocol and will comply with regulatory requirements. Local personnel will be trained on the InForm system. Access will be restricted to site personnel, trial managers, trial monitors and the data management team. Personnel will have individual log-on and passwords. It will be the investigator’s responsibility to ensure the accuracy of all data entered and recorded in the eCRFs. Trial monitors will check the accuracy of the eCRF data against source documents. It is anticipated that the majority of source data (medical progress notes and letters, tests and investigations) will be filed in the individual patients’ medical records. Any deviation from source data being present in the medical notes will be identified and documented. The eCRF and source documents must be available at all times for review by the sponsor’s clinical trial monitor, auditors and for inspection by the Medicines Health Regulatory Agency. The accuracy of eCRF data will be verified by review of the source documents and details will be provided in the Trial Monitoring Report.

### Statistical analysis

Before starting the data analysis, the level and pattern of the missing data in the baseline variables and outcomes will be established by forming appropriate tables. The likely causes of any missing data will be investigated. This information will be used to determine whether the level and type of missing data have the potential to introduce bias into the analysis results for the proposed statistical methods, or to substantially reduce the precision of estimates related to treatment effects.

The potential effects of performance, attrition and evaluation bias associated with the lack of a placebo arm will be considered. Although we are not able to fully exclude bias in the patient-reported outcomes, this will be minimised by exploring correlations between the primary endpoint and secondary outcomes, including analysis of SenseWear Armband activity monitors, to assess the possibility that a placebo effect is associated with evaluation bias. Attrition bias should be minimised by the fact that there will be no change in dosing for the duration of the trial, and we do not expect there to be any toxicity from the use of ambulatory oxygen. Subjects will be withdrawn from the trial only if they wish to do so or because of disease progression and the development of hypoxia at rest. We do not expect there to be any bias in the background provision of care (performance bias) depending on use or not of oxygen, as patients enrolled into the trial will be those not expected to change their treatment for the duration of the study.

Although we will not adjust for baseline K-BILD score in the primary analysis, secondary analyses using the K-BILD filled in at baseline visit (week 0) as a covariate, or mean of the K-BILD score at screening visit (week −2) and at baseline visit (week 0) will be considered.

### Primary outcome measure

The primary outcome will be the difference in K-BILD score on oxygen compared to no oxygen. We will use a generalised linear model with the difference in health status as the independent variable and treatment sequence as a covariate. If the assumption of the mixed model is not met, data will be either log-transformed and/or other nonparametric methods will be considered. Any adjusted analyses will be performed as secondary sensitivity analysis including adjusting for any covariate that is itself linked to the primary outcome (see below)Analysis of the primary outcome will be by intention-to-treat. The data will be analysed according to the initial randomisation groups irrespective of subsequent withdrawals. However, should there be a sizeable frequency of protocol variation, per protocol analysis will also be performedThe hypothesis to be tested is that ambulatory oxygen improves health status compared to no treatment. The study will be considered positive if statistical significance at the level of 0.05 (two-tailed) is achievedo Sensitivity analyses will include adjustment for any covariates linked to the primary outcome. These may include baseline K-BILD measurement, age, gender, smoking history, Body Mass Index (BMI), ILD severity as measured by the Composite Physiologic Index (CPI), presence of PH as measured by echo, baseline BNP levels, etc.o Patient-reported consumption of oxygen cylinders will also be factored in as a covariate. Its validity will be checked against oxygen company-reported cylinder consumption wherever possible, and, in a subgroup of patients, by direct observation by clinical nurse specialist (CNS) home visits (Aintree centre)o To assess the relationship between the response to supplemental oxygen measured with a series of parameters during the placebo air versus oxygen 6MWT and the benefit seen in day-to-day life with ambulatory oxygen, to identify any baseline predictors of responsiveness. These parameters will be included in the statistical model as fixed- effect variables. Possible 6MWT predictors to be analysed will include area under the curve of oxygen saturation, walked distance, maximum/minimum and mean heart rate, end-test dyspnoea, end-test oxygen saturation, end-test heart rate, and recovery times to baseline dyspnoea, heart rate and saturationo Exploratory sensitivity analyses of the effects of ambulatory oxygen will be conducted in predefined subgroups, including:
▪ IPF versus non-IPF▪ Patients with and without evidence of PH▪ Patients stopping and not stopping during the baseline 6MWT on air

STATA software will be used for statistical analysis

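### The planned sensitivity adjustment for patient-reported oxygen consumption conditions on a post-randomisation measure that exists only on oxygen, so it does not test the robustness of the treatment effect

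*Protocol article*

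**What the plan says.** Under Statistical analysis, Primary outcome measure, the protocol article defines the primary model: "We will use a generalised linear model with the difference in health status as the independent variable and treatment sequence as a covariate". I read the within-patient K-BILD difference as the outcome of that model. The same section says that "Analysis of the primary outcome will be by intention-to-treat" and gives adjusted analyses a lower status: "Any adjusted analyses will be performed as secondary sensitivity analysis including adjusting for any covariate that is itself linked to the primary outcome". Statistical analysis adds "Although we will not adjust for baseline K-BILD score in the primary analysis".

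The list that follows names possible adjustment covariates: baseline K-BILD, age, gender, smoking history, BMI, disease severity, pulmonary hypertension and BNP. These may be included. The next item is firm: "Patient-reported consumption of oxygen cylinders will also be factored in as a covariate". It goes on to the checking of reported use against company records and home visits. It does not say how use is coded or centred, or how the adjusted treatment effect is to be read.

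The Intervention section shows when use is measured: "To determine oxygen use during the 2 weeks when patients are randomised to be on treatment, patients will be asked to keep a daily diary". For patients who start on oxygen, "the company will be asked to remove any unused oxygen cylinders on the day of the crossover to the 2 weeks" off oxygen. A separate section treats cylinder counts as an assessment of compliance. Secondary outcomes are to be analysed by similar methods.

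**The concern.** A sensitivity analysis should estimate the same treatment effect under different assumptions. The other named covariates describe the patient or the disease, and adjusting for baseline values of them leaves the target as it is. Oxygen consumption differs in three ways:

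- It arises after randomisation.
- It has no counterpart off oxygen, where it is zero or undefined.
- It plausibly lies on the path from allocation to K-BILD, and may also reflect how well the patient feels and whether oxygen seems to help.

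Holding it fixed can remove the effect that the trial sets out to detect. A benefit that comes from using oxygen could seem to vanish on adjustment and be taken as a sign that the primary result is fragile. The wording on secondary outcomes could carry the same covariate into those models.

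**Working it through.** **Inputs from the protocol (Sample size estimate; Primary outcome measure).** Difference 8, SD 20, 90% power, two-sided 5%, 15% dropout, 80 randomised.

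**Assumptions of mine.** The protocol gives no distribution of use. I take mean 6, SD 3 cylinders as the main case and vary it.

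**1. The plan's own figure.** With SD 20 read as the SD of the within-patient difference, a paired t-test needs n = 68 (power 0.902), and 68/0.85 = 80. The stated size is reproduced. The unadjusted standard error is 20/√68 = 2.43.

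**2. What the covariate does.** Let D be the oxygen-minus-no-oxygen difference and S the centred sequence. In D = α + γS + ε, the intercept α is the treatment effect. Adding use U gives D = α* + γS + βU + ε. With balanced sequences, approximately:

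- α* = mean(D) − β × mean(U), the predicted difference at zero use;
- SE(α*) ≈ (σ/√n) × √(1 + mean(U)²/SD(U)²).

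**3. Benefit proportional to use.** β = 8/6 = 1.33, so α* = 8 − 1.33 × 6 = 0. In 4,000 simulated trials the adjusted term averages 0.0 against 8.0 unadjusted, and is significant in 5% of trials against 89%.

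**4. Benefit unrelated to use.** β = 0, so α* = 8, but SE ≈ 2.43 × √(1 + 36/9) = 2.43 × 2.24 = 5.4. The simulated SE is 5.6. Power is 31% from the formula and 29% simulated, against 90% unadjusted.

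**5. Range over assumed use, benefit unrelated to use (formula in step 2).**

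| Mean / SD of use | SE of α* | Power |
|---|---|---|
| 6 / 1.5 | 10.0 | 12% |
| 6 / 3 | 5.4 | 31% |
| 6 / 5 | 3.8 | 55% |
| 10 / 4 | 6.5 | 23% |

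Simulation with negative use set to zero gives 13%, 29% and 46% for the first three rows. With mean 10, SD 4, simulation gives SE 6.7 and power 23%. With proportional benefit the adjusted term averages about 0 in every simulated case (6/1.5, 6/3, 6/5 and 10/4).

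**6. Confounded use.** Take use 10/4, an effect that runs wholly through use (8/10 = 0.8 per unit), and heavier users doing worse by 8 points per SD of use. The fitted slope is 0.8 − 8/4 = −1.2, so α* = 8 + 1.2 × 10 = 20 (simulated 20.3). The total effect is 8 and the true zero-use effect is 0. The term is then an extrapolation that estimates neither.

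**7. Does the model format matter?** In a long-format model with U = 0 off oxygen, the within-patient difference in use is again U. In one simulated data set the treatment coefficient was 11.13 in both formats. Centring on the grand mean over both periods subtracts the same constant twice, and the coefficient stayed at 11.13.

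**8. Does centring on the on-oxygen mean matter?** Yes. Mean(U) is then 0, so α* = mean(D). In the same data set the adjusted and unadjusted estimates were both 10.42. In the 6/3 simulations the estimate is 8.0 and the SE 2.4 either way.

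**The case against.** Three arguments weigh against the point.

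First, the primary analysis has sequence as its only covariate. A reader might infer from the section heading that consumption enters the primary model. The text does not support that: adjusted analyses are made secondary, and the cylinder item follows directly on the sensitivity list. This stands. The primary test, the two-tailed 0.05 rule and the sample size do not involve use.

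Second, the zero-use reading depends on a coding that is not stated and may be fixed in an analysis plan that is not shown. Uncentred age or BMI would also give a meaningless intercept in the difference model. This stands as far as it goes: the losses in steps 3 to 5 of the working hold only for uncentred use or zeros off oxygen. The parallel with age is incomplete. A baseline covariate is constant within a patient and, once centred, can be adjusted for without changing the target. Use is present in one period only, so in a long-format model it competes directly with the treatment term, and grand-mean centring does not cure this.

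Third, the item may be meant as a dose-response analysis, and the remedy below uses nearly the same regression. That reading is possible, since the item goes on to validate reported use. But the text calls consumption a covariate alongside patient characteristics and does not label the analysis as non-randomised. No coding of use turns this model into a robustness check on the treatment effect. Nor does centring make the slope on use causal.

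The document does not say that an adjusted result would override the primary one. Misreading is a risk, not a stated plan.

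**Conclusion.** The point holds as a defect in the secondary sensitivity analyses. The protocol commits to adjusting for a measure that exists only on treatment and plausibly mediates the effect. Depending on coding, the adjusted treatment term is either an extrapolation to zero use or the unadjusted estimate over again. Neither tests robustness.

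In the first case, with 68 completers, an SD of differences of 20 and assumed use of 6/3, the term averages about 0 instead of 8 when benefit is proportional to use. When benefit is unrelated to use, its SE is about 5.5 instead of 2.4 and power is about 30%. These sizes are illustrative, because the use distribution is assumed: over the cases tried, power with unrelated benefit runs from 12% to 55%.

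The stronger claim, that adjustment necessarily yields the effect at zero use, is not supported, because centring on the on-oxygen mean avoids it. The confirmatory result is not at risk, so this should be corrected but is less than a must-fix.

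**What to change.** Remove oxygen consumption from the covariates of every model that estimates the treatment effect, for the primary outcome and for the secondary outcomes analysed by similar methods. Report it descriptively as compliance, together with the planned checks against company records and home visits.

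If the relation between use and benefit is of interest, specify it separately: a regression of the within-patient K-BILD difference on use, centred at its on-oxygen mean. Label it exploratory and non-randomised, and interpret the slope as an association only.

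The cost is a change of wording. The data collected, the primary analysis and the sample size stay as they are.
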